### Measurements

Baseline and discharge data were collected from patients and caregivers in person by a research Geriatrician and from the patients’ clinical records. Baseline patient characteristics were evaluated 15 days pre-hospitalization by asking retrospectively the patient or their caregivers/families/legal representatives when necessary. Follow-up data were collected by the researchers by telephone at 30 and 90 days after discharge in order to know their health status (Table 1).

**Table 1 Tab1:** Scheduled visits and activities

	**15 days pre-hospitalization**	**Baseline**	**Discharge**	**30 days post-discharge**	**90 days post-discharge**
Sociodemographic data		X			
Clinical data on admission		X			
Clinical data at discharge			X		
Conditions during admission			X		
Follow-up outcomes (mortality, number of visits to Primary Care physician or Nurse, Emergency Department visits, falls, and hospital readmissions)				X	X
Holden Functional Ambulation Classification (FAC)		X			
Charlson Index		X			
Barthel Index	X	X	X	X	X
Reisberg Global Deterioration Scale (GDS)	X				
FRAIL instrument	X	X	X	X	X
SARC-F scale	X				
Mini Nutritional Assessment- Short Form (MNA-SF®)		X			
Short Physical Performance Battery (SPPB)		X	X		
Hand grip strength (kg)		X	X		
Laboratory results on admission		X			
Ultrasound measurements		X	X		
DXA data		X	X		
Semi-quantitative intake questionnaire		X	X		

### Independent variables

Demographic, social, and anthropometric data: date of birth, sex, weight, height, body mass index (BMI), ethnicity, lives alone or accompanied, lives at home or in a long-term care. We will use these variables as control ones.Holden Functional Ambulation Classification (FAC) [25] is a functional assessment classification of gait ability, that quantifies the degree of gait dependence from 0 (totally dependent and unable to walk alone) to 5 (totally independent walking). This variable will be used as inclusion criteria.Charlson Comorbidity Index: this is a system for evaluating life expectancy at 10 years, depending on the age of the subject being evaluated and the comorbidities present [26]. It consists of 19 items (apart from age), which if present influence the subject's life expectancy. Initially it was adapted to assess survival at 1 year, but later in its final form it was adapted to assess survival at 10 years [27]. Each item has a given score, and the sum establishes the degree of comorbidity. In general, absence of comorbidity is considered to be 0–1 point, low comorbidity, 2 points, and high comorbidity equal to or greater than 3 points. Survival at 10 years is calculated using calculators [28]. This variable will be used in multivariate analysis as a control one.Clinical data not included in the Charlson index were recorded, including hip prosthesis, spinal estenosis or myelopathy, osteoporosis (or requires medication), vitamin D deficiency (or requires drug or nutritional supplementation), type of dementia if applicable (Alzheimer's disease, vascular or mixed), dyslipidemia (or drug required), insomnia (or requires medication), depressive syndrome (or requires medication), hearing deficit, complete deafness, significant vision loss, blindness, parkinsonism, epilepsy, and other relevant pathologies. This variable will be used in multivariate analysis as a control one.Main clinical diagnosis at the time of hospital admission. This variable will be used in multivariate analysis as a control one.Drugs prescribed up to the time of admission to the hospital. This variable will be used in multivariate analysis as a control one.Barthel Index: the Barthel index assesses basic ADL [29]. It is a hetero-administered questionnaire with 10 Likert-type items. The range of possible index values is between 0 and 100, with 5-point intervals, being the lower the score, the greater the dependence. This variable will be used to evaluate the secondary objective number 4.Reisberg GDS: it is the most widely used instrument to assess cognitive status and detect the presence of dementia of any etiology, although it was initially constructed to assess Alzheimer's disease [30]. It consists of 7 categories ranging from no cognitive impairment (GDS 1) to very severe cognitive impairment (GDS 7), and is evaluated by the physician. This variable will be used as inclusion criteria.FRAIL instrument: it is a simple frailty screening questionnaire developed by the Consensus Conference on Frailty working group and consists of 5 simple questions [31]. The answer can only be yes (scores 1 point) or no (0 points). 0 points indicates no frailty, 1–2 points prefrailty, and 3 or more points identify frailty. This variable will be used to evaluate the secondary objective number 4, and also as a control variable in multivariate analysis.SARC-F instrument: used for sarcopenia screening, understood as low muscle performance in the presence of a loss of muscle mass. It is a simple 5-question instrument, with three possible answers (score 0, 1 or 2 points) [32]. A score of 4 or higher is considered sarcopenia. This variable will be used to evaluate the secondary objective number 5.Short Physical Performance Battery (SPPB): developed by the National Institute on Aging, is an objective assessment tool for evaluating lower extremity physical performance in the older adult [33]. The SPPB consists of three tests: 1) hierarchical balance test, 2) short 4-m walk at usual pace, and 3) rising from a chair five consecutive times. Scores range from 0 (worst performance) to 12 (best performance). Low scores on the SPPB have high predictive value for a wide range of health consequences including disability in ADL, loss of mobility, hospitalization, length of hospitalization, nursing facility admission, and death. This variable will be used to evaluate the secondary objective number 4.Hand grip strength (kg) is an indicator of global strength, nutritional status, and predictor of changes in functionality in older adults. A digital JAMAR dynamometer was used. This assessment is performed seated in a chair, with shoulder and forearm in neutral position and elbow in 90 degrees of flexion. The position of the dynamometer was determined according to the size of the hand, allowing a comfortable and functional grip of the instrument with an adequate closure of the metacarpophalangeal and interphalangeal joints in the first position, favoring the contact between the first phalanx of the index finger and thumb. The participant performed a maximum grip force for 3 s, with 1 min rest between each repetition, making two attempts, where the best of both is the one that was used for the study [34]. This variable will be used to evaluate the secondary objective number 4.Eating Assessment Tool- 10 questionnaire (EAT-10®): this is a verbal, analog, unidimensional, direct-scored self-assessment scale to evaluate specific symptoms of dysphagia [35]. It is a 10-question questionnaire. The patient must respond to each question on a 5-point scale (0–4 points), with 0 indicating no problem and 4 indicating a serious problem. Higher scores indicate greater perception of dysphagia. This variable will be used to evaluate the secondary objective number 4.Mini Nutritional Assessment Tool—Short Form Questionnaire (MNA-SF®): this is a set of questions and measurements that assesses nutritional status in a simple way. It is a validated instrument where the highest score indicates normal nutritional status (12–14 points) and the lowest score indicates malnutrition (0–7 points) [36–38]. This variable will be used to evaluate the secondary objective number 4.A Semi-quantitative intake questionnaire was recorded daily in selected centers. This questionnaire determines daily the percentage of prescribed food that has been eaten in each meal of the day with five categories [all (> 80%), almost all (80–60%), half (60–40%), almost nothing (40–20%) or nothing (< 20%)]. It has to be performed by a dietitian, and calculates the mean of the complete hospital stay intake, to yield a final percentage of this intake [39]. This variable will be used to evaluate the secondary objective number 4.Lab tests data (in each center, usual admission lab parameters were used): hemoglobin, platelets, leukocytes, neutrophils, lymphocytes, albumin, total protein, total cholesterol (LDL and HDL if available), transferrin, ferritin, erythrocyte sedimentation rate (ESR), C-reactive protein (CRP), glycemia, creatinine, urea, thyroid hormones, creatin-phosphokinase, folic acid, and vitamin B12. These variables will be used to evaluate the secondary objective number 4.DXA was realized in selected centers (Horizon® DXA system, Hologic Inc., U.S.): variables included in the analysis were total muscle mass, appendicular lean mass (aLM), aLM/Body Mass Inex (BMI), aLM/height^2^, total fat mass, percentage of fat mass (%), start date, end date. These variables will be used to evaluate the secondary objective number 5.Patient conditions during hospital admission: number of days of bed rest, bed-chair, and with mobilization; number of days of rehabilitation, occupational therapy, and physical exercise; number of days fasting, liquid diet and basal diet. These variables will be used as possible explicative control variables for muscle changes during hospitalization.

### Muscle ultrasound measurements

Muscle Ultrasound measurements were acquired using a protocol previously validated [24], using a Chieson model ECO2 ultrasound system (Chieson Medical Technologies, Co. Ltd, Wimxu District Wuxi, Jiangsu, China) and a multifrequency linear-array probe (width of probe 38–58 mm). The patients laid supine in the bed with their arms supinated and knees extended and relaxed to full extension. The probe was coated with an adequate water-soluble transmission gel, and was aligned perpendicularly to the longitudinal and transversal axes of avQRF, with the aim of obtaining transverse and longitudinal images. The assessment was done without compression, because muscle dimensions change with contraction/relaxation, and the studied muscle is more compressible in a relaxed state. The acquisition site was located two-thirds of the way along the femur length, measured between the upper pole of the patella and the anterior superior iliac spine. Several images were registered of both QRF muscles for each measurement site. The image was stored pseudononymised on the ultrasound device computer.

The following measurements were acquired: first, we measured the cross-sectional area of the avQRF (mode b, in cm^2^); second, muscle thickness in longitudinal view (mode b, in cm); third, intramuscular central tendon thickness in mm, with an insonation angle perpendicular to the tendon; fourth, echogenicity of the muscle (1. normal; 2. heterogeneous; 3. fat infiltration; 4. atrophy due to fasciitis and necrosis); fifth, we scanned for the presence or absence of edema in the subcutaneous cellular tissue and the intramuscular and intrafascial fluid; sixth and last, we determined the presence or absence of muscle fasciculations using video testing [24].

New research has provided quantitative values and cut-off points of avQRF in older adults in different settings. In a cross-sectional study in 119 community-dwelling older adults from Siena (Italy), average avQRF thickness was 0.78 ± 0.26, significantly lower in sarcopenic patients (0.55 ± 0.2 vs. 0.9 ± 0.3) and females (0.7 ± 0.3 vs 0.86 ± 0.3), with a cut-off point of 0.7 cm for females and 0.9 cm for males to assess the presence of sarcopenia by ultrasound, sensitivity (S) 100%, and specificity (E) 64% [40]. In 857 community-dwelling adults aged 60 years and older from Thailand who were diagnosed with sarcopenia using the Asian Working Group for Sarcopenia-2019 algorithm, cut-off values of ≤ 1.1 cm of avQRF thickness were used for male and ≤ 1 cm for female (S 90.9%, E 92.2% for sarcopenia diagnosis) [41]. Another study in 204 community-dwelling older adults in Kyoto (Japan), showed mean values of avQRF of 2.91 ± 0.50 cm in men and 2.53 ± 0.44 cm in women. Best cut-off points for low skeletal muscle index were 2.88 cm for men (S 0.92, E 0.57) and 2.34 cm for women (S 0.66, E 0.75) [42]. A study in Sichuan (China) including 103 older adults at risk for sarcopenia according the Asian Working Group for Sarcopenia 2019 guidelines, showed a mean avQRF thickness of 2.97 ± 0.78 cm in men and 2.62 ± 0.71 cm in women [43]. Finally, a recent study in 40 older adults in a post-acute care unit in Barcelona (Spain) described a mean (SD) avQRF thickness of 1.49 (0.34) cm for men, and 1.32 (0.29) cm for women, and a avQRF cross-sectional area of 5.3 (1.3) cm^2^ for men, and 4.7 (1.5) cm^2^ for women [44]. We will compare our results with these previous data.

### Outcome measures

At discharge, mortality, length of hospital stay, and final clinical diagnosis were assessed. In addition, participants were followed-up by telephone 30 and 90 days after discharge, by the Geriatricians, to know their health status. Data were provided by the patients or the caregiver when needed. Vital situation and the following outcomes were recorded: falls (with or without fracture), disability in ADLs using the Barthel index, frailty using the FRAIL instrument, visits to the family physician and to specialists, visits to the emergency room, and hospital readmissions. Information was also compared with the electronic health records of the hospital.

### Bias

There could be a bias in the caption and measurements of the ultrasound images. To avoid these biases, geriatricians collecting the images received training by an expert radiologist before the inclusion of participants. In addition, all images were reviewed by an expert radiologist, who confirmed that the acquisition and measurements were correct.

### Data collection procedure

All patients or legal representatives and informal caregivers reviewed, signed, and dated the most current Institutional Review Board (IRB) approved written informed consent for participation in the study before any study-specific screening tests or evaluations were performed. Informed Consent Forms for enrolled patients and their informal caregivers, and for those who are not subsequently enrolled, will be maintained at the study site in compliance with the local data governance regulations.

All screening evaluations were completed and reviewed to confirm that a patient met all eligibility criteria before inclusion.

### Data collection methods

#### Data collection

Data collection was performed by the principal investigator and sub-investigators at each center. Inclusion and exclusion criteria were reviewed in the electronic clinical records at each center. A patient information sheet and informed consent was given to the patient. An evaluation was performed on admission, retrospectively 15 days prior to hospitalization, at discharge, and at 30 and 90 days after discharge as follow-up. All data were recorded in the patient's medical record and subsequently added to an electronic database. Before the study initiation, training was performed by all the researchers to harmonize the data acquisition. In addition, monitoring was conducted during the study procedures to improve adherence to the methodology.

#### Data management

Clinical data, including images, were pseudononymised and securely stored centrally in the electronic Case Report Form (eCRF) designed for this purpose, into a secure electronic Research Electronic Data Capture (REDCap®) [45]. Iidentifiable personal data were pseudononymized by assigning research numbers to the participants. All the investigators responsible for the study at their hospital sites received a personal username and password for the electronic database to handle the data with confidentiality. Access to the whole database was limited to the principal investigator.

### Data monitoring

The complete research team received training for the collection and storage of study data. The principal investigator, who had full access to the complete study registry, supervised the data continuously. The other investigators only had access to the patient registry of their hospital. The study coordinator, who was delegated by the principal investigator, conducted the monitoring.

### Sample size calculation

The main objective was to estimate quantitative parameters of avQRF, mainly the cross-sectional area values. As there were no previous normative data regarding muscle ultrasound values in hospitalized older patients, and also because our study was exploratory, we used information from previous research in Intensive Care Units to calculate the sample size. In the study from Baston et al., using Bland–Altman plots for inter-rater reliability, a measurement bias of 0.2 cm^2^ for the cross-sectional area of avQRF was described [46], allowing us to use this surrogate measure as the minimum significant value to detect real differences between measurements. Accepting an alpha risk of 0.05 and a beta risk of 0.2 in a two-sided test, 157 subjects were necessary to recognize as statistically significant a difference greater than or equal to 0.2 cm^2^ in the cross-sectional area of the avQRF. The standard deviation was assumed to be 0.8. It was anticipated a drop-out rate of 20%.

### Statistical methods

No value imputation system was established, so the final sample size was the number of patients with values at admission and discharge for the different parameters measured. We will determine the normal distribution goodness-of-fit of the continuous variables using the Kolmogorov–Smirnov and Shapiro–Wilk tests as needed. We will calculate the mean and standard deviations in the case of normally distributed variables and the median and the interquartile range in skewed variables. 95% confidence intervals will be calculated when necessary.

Variations between hospital admission and discharge ultrasound values, DXA and anthropometric parameters, functional scales, nutritional status, cognitive status, and in general any other quantitative variable, will be calculated using paired *t*-tests, Wilcoxon tests, or Mc Nemar chi-square tests when necessary.

The prevalence of sarcopenia will be calculated as percentages. Sensitivity and specificity of ultrasound measurements to determine sarcopenia will be calculated. Kappa analysis will be used to analyze the concordance between measurements. The coefficient of variation of the ultrasound device will be calculated. Sensitivity analysis will be conducted for each participating center. All analyses will be performed with SPSS (Statistical Package for Social Sciences) statistical software, version 24.0 or later (IBM Corp. Released 2016. IBM SPSS Statistics for Windows, Version 24.0. Armonk, NY: IBM Corp).

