## Background

The human aging process involves a decrease in lean mass together with a parallel increase in fat mass [1]. The skeletal muscle system from the third decade of life onwards, undergoes a slow but progressive loss of muscle mass and strength, a circumstance that is accentuated from the age of 65–70 years [2]. From the age of 50, muscle mass decreases by 1–2% annually, and muscle strength by 1.5–3% [3]. In men the process is more progressive, while in women there is an abrupt decrease coinciding with the menopause [3]. This process of loss of muscle mass was defined as sarcopenia [4], and since 2016 it is recognized as an independent condition by an International Classification of Disease, Tenth Revision, Clinical Modification (ICD-10-CM) Code (code M62.84) [5].

Although a consensus global definition of sarcopenia is still evolving [6], the European Working Group on Sarcopenia in Older People (EWGSOP) considers it as a “muscle disease (muscle failure) rooted in adverse muscle changes that accrue across a lifetime. Low muscle strength is the key characteristic of sarcopenia, the detection of low muscle quantity and quality in used to confirm the sarcopenia diagnosis, and poor physical performance is indicative of severe sarcopenia” [7]. This lack of consensus must not hinder the importance of diagnosing and treating sarcopenia in clinical practice [6, 8], because of its demonstrated association with falls and fractures, disability in activities of daily living (ADL), frailty, mobility disorders, cardiac and respiratory diseases, cognitive impairment, institutionalization, quality of life, healthcare costs, and death [7, 9–12].

Several tools are being used for the assessment of muscle mass and quality, including bioelectrical impedance analysis (BIA), magnetic resonance imaging (MRI), computed tomography (CT), dual energy x-ray absorptiometry (DXA), and ultrasound imaging. Recent publications present that ultrasonography may be a valid and reliable imaging method for the assessment of skeletal muscle mass [13–15].

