## Methods/design

### Objectives

The main objective of the study is to estimate, by means of portable ultrasound, parameters of muscle quantity and quality of the anterior vastus of the quadriceps rectus femoris (avQRF), including muscle area, thickness, and echostructure, in older adults hospitalized in AGUs for medical reasons.

Secondary objectives are 1) to determine the prevalence of sarcopenia on admission, using the EWGSOP-2 criteria [7], 2) to determine the incidence of sarcopenia on discharge, 3) to assess the evolution of muscle mass of the avQRF between admission and discharge, 4) to evaluate changes in nutritional status, lab results, hand grip strength, gait speed, ADL, frailty, and physical performance from admission to discharge, and at 30 and 90 days for ADL and frailty, and their relationship with ultrasound muscle measurements, and 5) to analyze the relationship between ultrasound muscle measurements and other methods of muscle assessment like DXA or SARC-F. These analyses will help in the validation process of ultrasonography for muscle mass and quality assessment.

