### Participants

Patients admitted to an AGU of the 7 participating centers between May 2019 and January 2022, meeting the inclusion criteria: (i) Age ≥ 69 years, (ii) Holden's Functional Ambulation Classification Scale level 1 or higher, and (iii) Informed consent signed by the patient or legal representative.

Exclusion criteria were: (i) Terminal condition or life expectancy of less than 6 months, (ii) impossibility or refusal to undergo muscle ultrasound, (iii) refusal for follow-up, (iv) severe dementia stage, with a Reisberg´s Global Deterioration Scale (GDS) scoring 7, and/or (v) impossibility in the opinion of the investigators to complete the necessary procedures of the study.

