## Discussion

Measurement of muscle mass and function, and thereafter, identification of sarcopenia, is a challenge in hospitalized older adults [47], and multiple studies have demonstrated that it is a disease with clinical relevance in this population, associated to severe clinical outcomes [7, 9–12]. Sarcopenia is frequent in hospitalized older patients, a vulnerable population to this condition that may be present on admission or developed during hospitalization because of hospital-associated immobility [48].

In addition, sarcopenia research is difficult in complex real-world old patients, because usually they are unable to collaborate with clinical, functional, and imaging testing [47]. Measurement of grip strength, and physical function tests like gait speed, the Timed Get Up and Go test, the 5-sit-to-stand test, or the SPPB, all of them necessary to implement sarcopenia criteria [7], may be very difficult to complete in many inpatients. Moreover, DXA, BIA, CT or MRI measurements may be unaccesible to many of them. The procedure with the overall highest completion rates in a recent cohort study was ultrasound measurement of the quadriceps muscle [47]. This technique provides non-invasive, real-time assessment of muscle quantity and quality, is highly acceptable to participants, and is associated with low perceived burden when compared to other testing [49]. Ultrasound measurement of avQRF has excellent inter-rater and intra-rater variability [50, 51], and has been proposed by EWGSOP-2 for clinical assessment of sarcopenia. Different protocols for ultrasound measurements have been proposed, although final consensus is lacking, while standardization is necessary [16, 24, 51–53].

Ultrasound technology has previously demonstrated validity and reliability for muscle mass and quality assessment [13–16, 19, 20, 54–56]. In our study we used a new simple protocol that has been previously described and validated in young adults in ICU patients [24], able to quantify muscle quantity and quality. In addition, we will be able to provide associations with DXA values and physical function tests. Added value of our study will be the multicenter and longitudinal design, and the ultrasound testing acquisition by previously trained geriatricians instead of radiologists, supporting the real-life use of this technique.

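### The complete-case rule, if applied to admission sarcopenia prevalence and ultrasound accuracy, drops patients without a strength value and probably understates prevalence

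*Protocol article*

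**What the plan says.** Under Objectives, the first secondary objective is "to determine the prevalence of sarcopenia on admission, using the EWGSOP-2 criteria". The Background cites the definition on which this rests: "Low muscle strength is the key characteristic of sarcopenia", with low muscle quantity or quality needed to confirm the diagnosis.

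The Discussion lists grip strength, gait speed and several physical performance tests and describes them as "all of them necessary to implement sarcopenia criteria [7], may be very difficult to complete in many inpatients". It also says of complex older patients that "usually they are unable to collaborate with clinical, functional, and imaging testing".

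Participants admits patients at "Holden's Functional Ambulation Classification Scale level 1 or higher" and excludes dementia only at the most severe GDS stage. It also excludes patients who, in the investigators' opinion, could not complete the study procedures.

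Statistical methods gives one rule for missing values: "No value imputation system was established, so the final sample size was the number of patients with values" at both admission and discharge, applied parameter by parameter. On the prevalence itself it says only this: "The prevalence of sarcopenia will be calculated as percentages". Sensitivity and specificity of ultrasound for sarcopenia follow in the same paragraph. No denominator is given for either analysis.

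**The concern.** A patient can be classified only if strength is known. The article expects the strength and performance tests to be hard for many of the patients it studies, yet the only rule it states keeps patients who have values. Under that rule, a patient with no grip or performance result at admission leaves both the numerator and the denominator of the prevalence. The same patient has no reference status and cannot enter the sensitivity and specificity table.

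This loss is unlikely to be random, because failure to perform a strength test is often a sign of low strength. The accuracy of ultrasound would then be estimated mainly in the fitter patients, whereas the Discussion's case for ultrasound is that it can be completed where other tests cannot.

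The rule's wording adds a second loss. It asks for a discharge value as well, which an admission prevalence does not need. Taken literally, it also removes patients who died in hospital or were not retested, although mortality at discharge is one of the listed outcomes.

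**Working it through.** **1. The plan's own figure.** The article gives no figure for prevalence precision or for missing strength data. Its only calculation is the sample size for cross-sectional area (two-sided alpha 0.05, power 80%, SD 0.8, difference 0.2 cm², drop-out 20%):

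- evaluable n = (0.8 × 2.8016 / 0.2)² = 125.58
- recruited n = 125.58 / 0.8 = 156.98, i.e. 157

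The stated 157 is reproduced. It concerns the area comparison and says nothing about prevalence. The 20% drop-out allowance is not a forecast of how many patients cannot be tested for strength.

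**2. Bias formula.** Let u be the share of enrolled patients with no status, p_able the prevalence in those with a status, and p_unable the prevalence in those without.

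- full-cohort prevalence = (1 - u) × p_able + u × p_unable
- complete-case estimate = p_able
- bias = p_able - full-cohort prevalence = -u × (p_unable - p_able)

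**3. Inputs.** The article gives neither u nor p_unable. Its only prevalence range, in the Background, is 10% to 40% across settings. Assumptions: p_able = 30%, p_unable = 50% to 90%, u = 10% to 30%.

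| u | Full-cohort prevalence | Reported | Bias (points) | Bounds: all without status non-sarcopenic / all sarcopenic |
|---|---|---|---|---|
| 10% | 32% to 36% | 30% | -2 to -6 | 27% / 37% |
| 20% | 34% to 42% | 30% | -4 to -12 | 24% / 44% |
| 30% | 36% to 48% | 30% | -6 to -18 | 21% / 51% |

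For u = 20%:

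- full-cohort prevalence = 0.8 × 0.30 + 0.2 × 0.50 = 0.34, and 0.8 × 0.30 + 0.2 × 0.90 = 0.42
- bounds = 0.8 × 0.30 = 0.24, and 0.24 + 0.20 = 0.44

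**4. Against sampling error.** With u = 20%, 157 × 0.8 = 125.6 patients have a status. The standard error is √(0.30 × 0.70 / 125.6) = 0.041, so a bias of 4 to 12 points is about 1.0 to 2.9 standard errors.

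**5. Other inputs.** With p_able = 25%, u = 20% and p_unable = 45% to 80%, the full-cohort prevalence is 29% to 36% and the bias is -4 to -11 points. The 95% half-width is 1.96 × √(0.25 × 0.75 / 125.6) = 7.6 points.

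**6. Direction.** If p_unable = p_able, the bias is zero for any u. If p_unable is half of p_able (12.5% against 25%, u = 20%), the bias is -0.2 × (0.125 - 0.25) = +2.5 points. The sign therefore depends on an input that the article does not supply.

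**The case against.** The strongest reply is that the rule is written around paired values. It speaks of admission and discharge, parameter by parameter, and the paired tests follow directly. Prevalence is mentioned separately with no denominator, so extending the rule to it is an inference. This is why the point is conditional. Still, no other missing-data rule is stated, and an analyst following the article would have only this one to apply.

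A reader might infer that prevalence is definitely biased downward. The documents do not support that:

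- They give no untestable rate, and the downward result comes from assuming p_unable above p_able.
- Inability can reflect cognition, poor cooperation or acute illness as well as weakness.
- Low strength alone does not make a case, because muscle quantity or quality must confirm it.
- The Discussion says that the tests may be very difficult, as general background. It does not say that patients in this cohort cannot do them. Grip is tested seated, so a low walking category does not by itself imply a missing grip value.

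Eligibility also matters. The exclusion for inability to complete procedures, and the walking criterion, remove some of these patients before enrolment. For them the consequence is a narrower study population, which no analysis of enrolled patients can repair. To that extent u among enrolled patients is smaller.

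Finally, the article does not say that inability is recorded as missing. The SPPB has a floor of 0, although the article does not state that inability scores 0 and gives no such rule for grip. A reader might also want chair rise to replace a missing grip value, but the article states no such substitution, so it is not proposed here. How inability is coded may be set out in a fuller document. What remains is the effect of the stated complete-case rule.

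**Conclusion.** The point holds as a conditional risk. If the stated complete-case rule is used for admission prevalence and for ultrasound accuracy, patients without a strength value are lost and, on a literal reading, so are those without a discharge value. Underestimated prevalence is the more plausible direction but is not established.

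The illustrative -4 to -12 points rests wholly on the assumed 20% untestable share and the assumed prevalences of 30% and 50% to 90%. At the upper end it would exceed the sampling error. No size is given for the effect on sensitivity and specificity, since the article offers nothing from which to derive one.

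Prevalence is a secondary objective of an exploratory study, so this should be corrected in the analysis but does not undermine the main objective.

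**What to change.** For the admission prevalence and the accuracy analysis:

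1. Base admission prevalence on all enrolled patients, whether or not they have discharge values. Keep the paired rule for the admission-to-discharge comparisons.
2. Report the number without a sarcopenia status, with reasons where recorded. Separate missing strength from missing muscle mass: DXA was done only in selected centres, so if it supplies the confirming measure, some patients will lack a status for reasons unrelated to weakness.
3. Give lower and upper bounds for prevalence, counting all patients without a status first as non-sarcopenic and then as sarcopenic.
4. Where physical inability was recorded, add a sensitivity analysis of prevalence and accuracy that counts it as low strength, with muscle mass still needed to confirm. Keep refusal, poor cooperation and technical failure as missing.

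This needs changes to the analysis wording and some recoding, and no new measurements. Step 4 is possible only where the reason for non-performance was captured, which the article does not show. The price is wider reported uncertainty, and possible misclassification of patients who could not perform for reasons other than weakness.
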